## Abstract

**Background:**

Nursing in palliative medicine combines primary patient care with the special challenges of this medical field (eg, handling the processes of dying, grief, and death). These cause high stress levels and burden on the nursing staff, resulting in an early exit from working life because of physical or psychological disorders like burnout.

**Objective:**

DiPa (digitally identifying and minimizing stressors in palliative care) is a prospective study investigating the feasibility of measuring burden and its causes in palliative care using methods of subjective and objective stress detection. Based on these results, stress-reducing interventions are to be deduced and evaluated. In this paper, we present our study protocol.

**Methods:**

The nursing staff of an inpatient university palliative hospital ward gathered data over 6 weeks. Each was equipped with a smart wristband and a smartphone that continuously measure physiological and ambient parameters throughout their working day. These objective data were enriched by subjective measurements: a questionnaire at the beginning of the study that assessed multiple potential stressful situations and constellations in the private and working environment as well as ecological momentary assessments (EMAs) during the workday. The EMAs were prompted by scanning near-field communication (NFC) tags placed at different locations on the ward. The ongoing data analyses will be processed using computer algorithms partly programmed specifically for this study and partly drawn from existing libraries, such as toolboxes for neurophysiological signal processing for Python. Comparisons between subjective and objective measures and group comparisons between variables of interest will be made using inferential statistics, including regression analyses and analyses of variance. Data analysis using machine learning algorithms will be implemented once sufficient data are gathered.

**Results:**

The study was funded in October 2019. As of July 2025, 12 of 18 nurses in the palliative care unit consented to participate in our study. We expect to start detailed data analysis in in the third quarter of 2025 and to finish and publish our results in 2026.

**Conclusions:**

The DiPa study aims at testing the feasibility of measuring and merging subjective and objective stress parameters for palliative care nurses.

**Trial Registration:**

German Register for Clinical Studies DRKS00024425; https://drks.de/search/en/trial/DRKS00024425/details

**International Registered Report Identifier (IRRID):**

DERR1-10.2196/63549

## Introduction

### Background

Chronic and severe diseases are increasing in importance and require sufficient medical treatment and well-educated specialists in the field to provide medication, help with personal hygiene, and offer counselling. In 2020, 1.7 million nursing staff worked in nursing and older adult care in Germany [1], which reflects a growing shortage of skilled workers in view of the aging population. The reasons are manifold, but the reasons found in the working environment include the 3-shift system, time pressures, and heavy physical and emotional burden, leading to dissatisfaction or even leaving the profession [2,3]. These factors can be found in almost all hospital departments but are exacerbated in areas with a high level of physical and interpersonal care. Palliative medicine is one of these particularly sensitive areas.

### Palliative Medicine

Palliative medicine is a specialty for the treatment of people with critical diseases like advanced cancer or higher-grade cardiac, renal, or lung diseases with limited life expectancy. Palliative care is a challenging discipline, not only due to the required medical care but also due to the psychosocial and spiritual aspects in the interaction between nursing staff and patients or their relatives, especially given the aim of improving quality of life in the last months and weeks of the patients’ lives. The main tasks of nursing staff in the palliative field include life support for the terminally ill and relieving their suffering from commonly experienced severe symptoms. These include pain, shortness of breath, and nausea, as well as anxiety and depression, which are also highly prevalent, as Sewtz et al [4] showed in their study.

### Burden in Palliative Caregiving

Palliative nurses face many work-related stressors (like interruptions, time pressures, interpersonal conflicts, or shift work, as aforementioned) that are also experienced by other professions in addition to stressors that are unique to taking care of patients who are terminally ill or close to dying. Additionally, they are not able to express their needs, which can also lead to burden as Seibel et al [5] have published in 2024 (see Table 1, adapted from [6]). It is an imminent part of the job—physicians and palliative nurses are confronted with the end of a patient’s life and with patients and relatives facing this stage. Even though nurses in this field choose this sensitive job after careful consideration, it still is an emotional burden to cope with the dying and death of patients for 54% to 68% of nurses in palliative care [6], which is moderated by circumstances (eg, age of the patient, patient and caregiver agony).

**Table 1 table1:** Examples of potential stressors in a palliative care unit (PCU).

Factors	Examples
Team-associated factors	Staff fluctuation among physicians in the PCU Lack of support Lack of appreciation by other professional groups
Patient-associated factors	Young patients’ ages High care effort due to symptoms (eg, wounds, nausea, breathlessness, restlessness) Insufficient symptom control (eg, therapy-resistant pain, insatiable bleeding)
Structural factors	Understaffing High amount of documentation Inadequate education of patients and relatives about the palliative setting by the referring doctor
Personal factors	Ethical conflicts Feeling of being overwhelmed High expectation of one’s own work

Only a few studies have investigated this topic [6-12]. Diehl et al [11] surveyed and compared strains and resources for 149 nurses (34.5% response rate) working in the field of palliative care (in hospitals, hospices, or outpatient care in Germany). In their study, more than one-half of the nursing activities were perceived as heavy burdens, including transferring patients, time pressures, having to care for too many patients per day, handling patients with severe symptoms, and dealing with grief and death. Being surrounded by these topics every working day, nurses are at risk of psychiatric disorders that can accumulate to result in burnout syndrome in 15% to 20% of palliative nurses in home care [12,13].

Clinicians and researchers demand more studies, as urged by Pereira et al [10] in their systematic review of burnout syndrome in palliative care. Further evaluations of palliative care nurses throughout Europe could ensure better positioning of any results in the transnational context of the palliative care area and reveal further deficits in the care structure [9].

### Digitally Identifying and Minimizing Stressors in Palliative Care Study

The DiPa (Digitally Identifying and Minimizing Stressors in Palliative Care) study was conceptualized to use digital technologies (“Di”) to assess the working conditions of and burden on nurses in palliative settings (“Pa”). The study is a joint project of the Fraunhofer Institute for Computer Graphics Research (IGD) Rostock and the University Medical Centre Rostock (UMR) and funded by the State Office for Health and Social Affairs Mecklenburg-Western Pomerania. The study aims to identify correlations between measured objective physiological parameters and subjective perceptions of stress in everyday situations in the palliative care unit (PCU). Therefore, the primary goal is demonstrating the feasibility of identifying stressors in palliative care and measuring stress reactions with wearable devices. With these initial results, stressors and stress can be reduced by developing preventive measures.

### Physiological Stress Model

To explain our rationale for using wearable devices to measure stress in humans, we present the physiological stress model. The autonomic nervous system is responsible for all vital functions, regulating breathing, digestion, and the cardiovascular system as well as influencing the heart and glands [14]. The autonomic nervous system is divided into the sympathetic nervous system (SNS) and parasympathetic nervous system, which often act antagonistically. Although the SNS is activated by stress, the parasympathetic nervous system supports resting states. “Stress” occurs when the demands of the environment exceed the individual’s ability to cope [15]. It is defined as an individual’s reaction to burden and is caused by triggers that are called “stressors.”

Three phases of the physiological reaction can be distinguished. The phases were first described as part of the “general adaptation syndrome” by Selye and Köbcke [16]: The first phase is called the “alarm phase” and appears immediately after the stimulus.

The SNS reacts to a stressor by releasing catecholamines like noradrenalin and adrenalin from the adrenal medulla [17] and, simultaneously, adrenocorticotropic hormone from the cortical part of the brain [18]. In their paper, Chodan et al [19] described how the different physical changes interact during the alert: The muscles require oxygen for the oxidation of glucose and fat into energy. To provide this surplus of oxygen, breathing rate and heart rate (HR) increase. Empirical knowledge and experiences with handling data from biomedical parameters gathered with wearable devices have been accumulated in prior studies [19-21]. In particular, HR and heart rate variability (HRV) have been identified as valid stress markers [22,23].

To facilitate chemical reactions to provide energy (ie, the oxidization of glucose and fat), body temperature rises. At the same time, to protect the body from overheating, the sweat glands are also targeted by the SNS, increasing skin conductance and lowering skin resistance, which can be measured between 2 electrodes placed onto the skin [24]. Thus, measuring sweat secretion is an important method to investigate the activity of the SNS and to determine stress reactions.

Directly after the alarm phase, the “resistance phase” ensures and is biochemically characterized by increased cortisol liberation. Cortisol passes through the blood-brain barrier to the hippocampus, which then lowers the activity of the hypothalamic-pituitary-adrenal axis via negative feedback mechanisms. This serves to regulate stress reactions and prevent exhaustion of stress hormones.

Only in chronic stress (eg, when the available resources are insufficient to relieve stress or when the stressor is present over a long period of time), a third phase, “exhaustion phase”, follows, with symptoms of exhaustion and a dangerous weakening of the immunological system [25].

The DiPa study aims to test the feasibility of measuring and merging subjective and objective stress parameters in palliative care nurses.

In addition to physiological models of stress, various psychological frameworks have been developed to explain the conditions under which stress occurs in the workplace. One of the most widely known is the Job Demand-Control (JDC) model, originally proposed by Karasek [26]. This model posits that stress results from the interaction between the psychological demands of a job and the individual’s decision latitude, or control, over their work tasks. According to the model, high job demands combined with low control are particularly detrimental, leading to increased strain and adverse health outcomes.

It is important to acknowledge that the JDC model—and other cognitive-behavioral stress frameworks—can be meaningfully integrated with our somatic approach. All major stress models, despite differing in their conceptual emphasis (eg, cognitive appraisal, social support, or organizational structure), converge on the notion that stress elicits a biological stress response. Our focus on this common somatic end point allows for alignment with a broad range of theoretical models, including the JDC model. Specifically, job conditions characterized by high demands and low control, as described in the JDC framework, are likely to be present in the workplace of palliative care nurses and are thus likely to activate the very physiological stress pathways that are measured in this study.

## Methods

### Study Design

To assess the working conditions of and burden on nurses in palliative settings, preliminary tests were executed to investigate the functionality of and user experience with wearables, including handling in a hospital environment and resistance to the hospital’s disinfection routines.

The study design (Figure 1), a prospective cross-sectional approach with continuous measurements throughout each workday, allows for assessing both the current manifestation of stressors and current level of perceived stress load both objectively and subjectively. Participants were split into groups, and each group conducted the measurements for 6 weeks, thus expanding the span of the measurement across all participants (to increase the time frame depicted in the data), while individual participants were not burdened with the additional workload for longer than necessary.

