### Apparatus

#### Overview

Stress level was measured both objectively (physiological stress reaction) and subjectively (appraisal of the perceived stress in ecological momentary assessments [EMAs]). Possible stressors were also identified both as subjective perception via questionnaires and objectively by matching physiological stress responses to concurrent ambient conditions, such as noise, interruptions, or specific activities. We compared the objective stress levels to the daily staffing, occupancy level, and other daily changing factors of a hospital ward.

To this end, a combination of wearable and ambient sensors that can measure the physiological (objective) stress reaction as well as possible stressors (causes of stress) is being used. The prototypical setup consisted of a smart wristband, a smartphone, near-field communication (NFC) tags, and Raspberry Pis equipped with microphones to record interruptions (incoming telephone calls) and unexpected tasks (calls from patients). The setup can be seen in Figure 2 and Figure 3. At the end of the study, it will be possible to characterize a normal working day of a palliative caregiver more precisely in terms of physical and psychological stress. The perceived burden will be correlated with bed occupancy and the numbers of patient admissions, discharges, and deaths per day as well as influence of the duty roster design (including the staffing) and frequency of interruptions by telephone or a patient’s bell.

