### Sample and Recruitment

The PCU at UMR, with its 14 beds, is the largest PCU in Mecklenburg-Western Pomerania, Germany. It employed 13 full-time nurses and 5 part-time nurses who work in a 3-shift system during the study implementation in 2021. Study participants had to be older than 18 years, their working time had to have a minimum of 20 hours per week, they had to have proficiency in written and spoken German, and they had to be employed at the palliative care unit at the Rostock University Medical Centre (inclusion criteria). Exclusion criteria comprised of nonconsenting capacity and nonfulfilment of all inclusion criteria. For the DiPa study, all 18 nurses working in the UMR PCU, who partly specialize in palliative care, were invited in December 2020 to participate in the study by presenting the procedure and aims of the project in a lecture as well as in a written inquiry. The measurement period for each participant was 6 weeks allowing for a total measurement duration of 3 months.

A power analysis was not conducted as the population was prespecified (N=18), rendering the need for an accruing sample. In the end, 12 nurses agreed to participate, resulting in a participation rate of 67% (12/18).

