The acceleration data were fused to a 3D vector by applying the following equation:

All algorithms for data extraction were written in Python using Jupyter Notebooks and the *Pandas*, *Numpy*, *SciPy*, *Matplotlib*, and *NeuroKit2* libraries.

For stress detection analysis, all stress events marked with a button press will be identified, and windows surrounding this event will be extracted and averaged, leading to one value per stress event per participant. Analogously, the windows surrounding a scan of the NFC tag “relaxation” and the baseline windows will be extracted and averaged as well. Descriptive and inferential statistical analyses will be applied using IBM SPSS Statistics 30. Weighted ANOVAs for correlated samples will be computed to compare the stressful events and the baseline for each physiological parameter.

To examine the predictability of experiencing stress, the subjective ratings given in the EMA will be used as ground truth. Surrounding the EMA, data windows will be extracted from the data for each physiological parameter. A linear regression will be computed with the subjective stress level (EMA) as the dependent variable and entering the means of the physiological variables (HR, HRV, tonic EDA, phasic EDA, temperature, and acceleration) as independent variables. Artificial intelligence approaches will be used to analyze the data where appropriate.

With the data for daily occupancy of patients and the total number of nurses on the same day, we will be able to calculate the relationships of these 2 variables with stress. The minimum occupation level according to the recommendation from the German Society for Palliative Medicine (*Deutsche Gesellschaft für Palliativmedizin*) on staffing in palliative wards [30] of 1.4 nurses per patient will be used as a cutoff to create two subgroups of “well-staffed” and “under-staffed.”

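### Different nurses measured at different times, but the ward-condition analyses name no nurse or group term, so a chance difference between groups can pass for (or hide) an occupancy or staffing effect

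*Protocol article*

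**What the plan says.** Study Design: "Participants were split into groups, and each group conducted the measurements for 6 weeks". The stated purpose is a longer calendar span: "thus expanding the span of the measurement across all participants (to increase the time frame depicted in the data". Sample and Recruitment adds: "The measurement period for each participant was 6 weeks allowing for a total measurement duration of 3 months". Twelve nurses took part. The text does not give the number of groups, their sizes, their overlap or how nurses were assigned, and Figure 1 is not shown.

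Apparatus, Overview, plans the ward-condition analyses: "The perceived burden will be correlated with bed occupancy and the numbers of patient admissions, discharges, and deaths per day", along with the duty roster, staffing and interruptions. For the physiological side it says "We compared the objective stress levels to the daily staffing, occupancy level, and other daily changing factors of a hospital ward". Data Analyses returns to occupancy and the number of nurses on the day: "we will be able to calculate the relationships of these 2 variables with stress". It also splits the data into two staffing subgroups at 1.4 nurses per patient. None of these statements names a nurse, group or period term. The only within-person method in Data Analyses is the correlated-samples ANOVA of stress events against baseline, which does not cover ward conditions.

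Data Analyses and Ethical Considerations keep individual-level analysis at Fraunhofer IGD and pass only averaged data or group means to the university hospital (UMR).

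**The concern.** Momentary stress is a personal rating on a 0 to 100% slider, so its level can differ from nurse to nurse for reasons unrelated to the ward. Occupancy, deaths and staffing vary by calendar day. Because the groups cover different calendar time, a difference in average rating level between groups is linked to any difference in ward conditions between their periods. A correlation taken across the whole span then mixes two things: how a given nurse's stress moves with ward conditions, and how one set of nurses differs from another. Reducing the data to one mean per ward-day does not separate them.

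At stake are associations listed as secondary outcomes (Potential Outcomes and Impact) that are meant to lead to preventive measures (Future Directions). A chance group difference could point to staffing or occupancy wrongly or, with the opposite sign, hide a real relationship. The limitations section discusses reactivity, self-selection and the lack of stratification, but not the change of nurses over time.

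**Working it through.** The protocol gives no sample-size, power or alpha figure to reproduce ("A power analysis was not conducted as the population was prespecified (N=18"), so the check concerns the mechanism and its possible size.

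**From the document.** 12 nurses; 6 weeks per nurse; 3 months in total. Two back-to-back blocks give 2 × 6 = 12 weeks, against about 13 weeks in 3 months. Two successive groups therefore fit the text, but so do staggered groups.

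**Assumed, not in the document.** Two groups of 6; 42 days each (84 daily means); between-nurse SD 15 points (range 10 to 20); within-nurse SD 15; 3 rated nurses per day; no true effect; a 5% test.

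**Step 1: chance difference between groups.** SD of the difference in group means = SD_nurse × √(2/6).
- SD_nurse 10: 5.8 points
- SD_nurse 15: 8.7 points
- SD_nurse 20: 11.5 points

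**Step 2: how it reaches the slope.** Let D be the difference in group mean rating, s the shift in mean occupancy between periods, and v the within-period variance of daily occupancy. With equal periods, the spurious slope is D·s·0.25 / (v + 0.25·s²). Take D = 10 points and an occupancy SD of 1.5 beds, so v = 2.25:
- s = 0: 0
- s = 0.5: 1.25 / 2.3125 = 0.54 points per bed
- s = 1: 2.5 / 2.5 = 1.00
- s = 2: 5 / 3.25 = 1.54

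Simulated slopes were 0.55, 1.01 and 1.56 for the three non-zero shifts.

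**Step 3: false-positive rate over random groups.** Pearson correlation of the 84 daily means, 600 runs per cell, shift in units of the daily SD:

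| Between-nurse SD | shift 0 | 0.5 SD | 1 SD |
|---|---|---|---|
| 10 | 4% | 9% | 22% |
| 15 | 6% | 13% | 28% |
| 20 | 5% | 15% | 30% |

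Across repeat simulations under the same assumptions the ranges are about 8-15% at half an SD and 20-33% at one SD. Within-group centring gives 4-6%; a within-nurse estimate with day-clustered errors gives 5-8%.

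**Step 4: sensitivity.** A second set-up used 3,000 runs, a daily occupancy SD of 1.5 beds, each nurse on duty on half the days, and a smaller noise SD of 7.5 per nurse-day. It gave 17-22% at a shift of 1 bed, 29-38% at 1.5 beds (one daily SD) and 39-47% at 2 beds; within-group centring gave 4.0-5.7%. With between-nurse SD 15, the mean slope stayed near 0 at every shift. The SD of the slope rose from 0.72 (no shift) to 1.46 (2 beds), but stayed at 0.64-0.66 within group. In the first set-up at a one-SD shift and between-nurse SD 15, a 14-day overlap between two groups gave 18%, and three staggered groups gave 25%.

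**The case against.** The strongest reply is that this argues from silence. The ward-condition analyses are sketched in a sentence or two each, with no model, unit of analysis or covariate list. A plan that is not shown could include a nurse or period term, and Fraunhofer IGD holds the linked individual data needed for one. This stands in part: the text does not say that data are pooled across groups, nor does it rule out a nurse term. What remains is that the article fixes a grouped design, describes simple correlations and a two-way staffing split, and sets a data flow in which nurses are averaged before the data reach the university hospital. Once nurses have been averaged together, a within-nurse estimate is no longer possible there.

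A reader might infer that two panels of six replaced one another completely part-way through. The durations fit that, but the text does not state it. Overlap weakens the problem without removing it.

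A reader might also call this a systematic bias. It is not one over random groups: the expected slope error is zero, and the inflation is between-nurse variance left out of the analysis. It is confounding only for the particular groups drawn. It therefore overlaps with the general need to account for repeated ratings by the same nurse, although averaging to ward-days does not cure it.

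Finally, no passage reports that occupancy or staffing drifted, and the primary outcome is feasibility. Both points are correct and limit the weight of the finding.

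**Conclusion.** The point holds conditionally. By design, different nurses supply data at different times, and the ward-condition analyses as described do not separate nurse or group differences from ward effects. If average ward conditions also shift between the groups' periods, a chance difference in rating level can create or mask an association. Under the first set of assumptions in the working, false-positive rates are about 8-15% at a shift of half a daily SD and 20-33% at one SD, against about 5% within group. They are higher with quieter daily data and lower with overlapping groups. With no shift there is no inflation. These sizes are illustrations: group structure, variances, nurses per day, the shift and the 5% test are all assumed. The documents do not support saying that a distortion has occurred, and feasibility, the primary outcome, is not affected.

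**What to change.** For these secondary analyses, state that associations of stress with occupancy, admissions, discharges, deaths and staffing, including the comparison at the 1.4 cutoff, are estimated within nurse. Use nurse fixed effects, or centre stress and exposure on each nurse's own mean. Nurse effects also absorb the measurement group. Run this at Fraunhofer IGD on the individual-level data before averaging, with standard errors that allow for nurses sharing the same ward-day. If only averages can be shared, keep the group label, estimate the association within each measurement group, and combine the estimates. Report the number, size and calendar overlap of the groups alongside.

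The cost is an analysis change on data already collected, within the existing data-protection arrangement. Exposure differences between periods no longer contribute, so intervals widen somewhat. The change can be made together with any repeated-measures correction to the same analyses.
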